### Determination of sample size

The sample size was calculated using formulae presented by Hussey and Hughes.^17^ Assuming a baseline non-conveyance rate of 10% (from routine and feasibility study data)^8^ and a 10% point increase in non-conveyance with VAD, an intracluster correlation coefficient of 0.01 and 90% power at the two-sided 5% level of significance, we estimated that the 80 ambulance clusters will need to recruit a total of 800 participants (without repeat presentations) to the trial. The intracluster correlation coefficient was estimated to be 0.009 for non-conveyance for all reasons (not just SVT) using routine data from 94 SWASFT ambulance stations for care episodes for the 12 months between 1 February 2019 and 31 January 2020, inclusive.

Each ambulance cluster would be expected to recruit two participants in each of the five stages (each stage lasts 4 months) over the 20 months of recruitment. The target effect size was based on the minimum clinically meaningful effect that would justify a change in practice, taking into account the benefits and cost of the devices while remaining plausible according to the feasibility trial data (12% absolute increase in non-conveyance (95% CI: 3 to 34)).^8^ Prior to commencement of the trial, we also undertook a data collection exercise, using the proposed trial eligibility and data collection methods. This showed 63 (95% CI: 50 to 77) eligible patients had undergone a VM for SVT in SWASFT over 1 month. This number was in keeping with data from our feasibility study and previous service evaluations and in excess of that needed in our sample size estimates (40/month). This will allow for repeat presentations (around 10% of all cases by the end of an SVT VM trial of similar duration) and opt-out of data use, which, from our patient and public involvement and engagement and feasibility work, we expect to be low.

Due to the study design, recruitment will also largely be determined by normal practice rather than specific trial activities. It was felt that 20 months to recruit 800 participants is conservative and achievable. However, initial study progress criteria are proposed to monitor the recruitment rate (see table 2).

**Table 2 T2:** Study progression criteria

Criteria	Green	Amber	Red
Individual-level recruitment	≥160 participants (100+%)	128–159 participants (80–99%)	<128 participants (below 80%)
Cluster-level recruitment	80 (100%) clusters each recruit at least one participant	72–79 clusters each recruit at least one participant (90–99%)	<72 clusters each recruit at least one participant (below 90%)

Progression criteria after 4 months of participant trial recruitment.

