### Formation of ambulance station clusters and randomisation

Ambulance station clusters will be formed from the 93 SWASFT ambulance stations in existence at the time of study set-up. Recent historical data on activity and general conveyance rates for all stations were collected to inform the formation of trial clusters and sample size calculations. After merging very small and closely located stations, while maintaining the largest possible number of similar sized clusters, 80 (mostly single station) ambulance station clusters were identified. Clinicians working from these stations use equipment bags strictly belonging to and stocked by that station.

The stepped wedge trial design is comprised of five stages, with each stage lasting 4 months. In the first stage, none of the station clusters will have access to the VAD and patients will be treated as per standard practice. The clusters will then be randomly allocated, by computer-generated sequences (stratified by location and balanced on cluster size), to include VADs with their equipment bags, in one of the four remaining stages, so that 20 clusters and their clinicians receive access to the VAD for the first time at each stage. Randomisation will be performed by an independent statistician otherwise unconnected with the trial.

Once the VAD has been introduced, the cluster will retain the use of devices for the remainder of the study so that by the fifth stage, all 80 clusters and their clinicians will have access to the VAD (see figure 2). Devices will be added to a clearly marked ‘Valsalva pouch’ attached to the standard equipment bag. These bags are checked and restocked daily and carried by all treating ambulances. All station clusters randomised to VAD use will initiate availability of the VAD on the same day, coordinated by SWASFT supply logistics and the local ambulance station ‘champions’ (listed as trial collaborators). These processes will be overseen by the Clinical Trials Unit to ensure protocol compliance as far as possible. Ambulance stations will be notified of activation with sufficient time to enable Valsalva pouches to be changed and all station clinicians to be notified. No other individuals outside the Lead Research Paramedic, logistics supply chain and the station clinicians will be made aware of the randomisation.

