#### Progress (RAG) criteria

The stepped wedge design is predicated on reliably recruiting the number of participants specified by the sample size calculation at each stage of the trial. Monthly recruitment will be monitored closely by the TMG and regularly reported to the TSC. Recruitment below target (amber or red criteria) will trigger a remedial plan by the TMG with promotion of the SVT guideline and trial awareness and feedback on missed cases (where a VM was indicated but not undertaken) in addition to the planned promotion of the trial (newsletters, posters, etc) and NIHR CRN support. Financial constraints would preclude significant trial prolongation and if, despite these measures, trial recruitment was less than 80% of our overall target for the first 4 months of the study, we propose discussion with the TMG, TSC and funder to consider trial termination or agreed modification.

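### The cluster row of the progression criteria is not calibrated to a mean of two participants per cluster, so a trial on target would probably score red and almost never green

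*Protocol article*

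**What the plan says.** The section on formation of clusters states that "80 (mostly single station) ambulance station clusters were identified", formed "while maintaining the largest possible number of similar sized clusters". The section on sample size states that "we estimated that the 80 ambulance clusters will need to recruit a total of 800 participants (without repeat presentations) to the trial", and then: "Each ambulance cluster would be expected to recruit two participants in each of the five stages". A stage lasts 4 months, so the target for the first stage is 160.

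Table 2 applies two criteria after those same 4 months:

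- **Individual row:** green at 160 or more, amber at 128 to 159, red below 128.
- **Cluster row:** green only when all 80 clusters have at least one participant, amber at 72 to 79. The red cell reads "<72 clusters each recruit at least one participant (below 90" per cent).

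The section headed Progress (RAG) criteria gives the consequence: "Recruitment below target (amber or red criteria) will trigger a remedial plan by the TMG". The plan consists of promoting the SVT guideline, raising trial awareness and giving feedback on missed cases. Discussion of termination or modification is attached separately to overall recruitment below 80% of target in the first 4 months.

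**The concern.** The cluster row treats an empty cluster as a sign of trouble. With a mean of only two participants per cluster, some clusters will be empty by chance alone. If chance empties are common enough to push the count below 72, the two rows give opposite signals for the same on-target trial. The remedial plan would then start with no shortfall to remedy. A signal that is nearly always on also cannot pick out stations that are truly failing to recruit, which is presumably the purpose of the row.

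**Working it through.** **Plan's own figures.** 800 / 5 stages = 160 per stage; 40 per month × 4 = 160; 160 / 80 = 2 per cluster; 0.8 × 160 = 128; 0.9 × 80 = 72. These agree with each other. The total of 800 also reproduces with the Hussey and Hughes variance (80 clusters, 5 stages, 20 crossing at each step, 2 per cluster-stage, ICC 0.01) if the outcome variance is taken at the control rate, 0.1 × 0.9 = 0.09. The standard error is then 0.0304, power is Φ(0.10/0.0304 − 1.96) ≈ 0.91, and the total for 90% power is 777 to 785. Nothing below depends on that variance choice, only on the target of 160.

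**Assumption.** Cases fall at random across clusters. The article does not say so. It does say that recruitment will largely follow normal practice rather than trial activity, and it describes no mechanism that would spread cases evenly.

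**Equal clusters, 160 participants.**

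- Expected non-empty clusters = 80 × [1 − (79/80)^160] = 69.3. The Poisson version is 80 × (1 − e^−2) = 80 × 0.8647 = 69.2, so about 10.8 clusters are empty by chance.
- Exact distribution (160 participants placed one by one into 80 equally likely clusters): P(red) = 0.806, P(amber) = 0.194, P(green) = 8 × 10^−7.
- Poisson version: P(red) = 0.77, P(amber) = 0.23, P(green) = 0.8647^80 = 9 × 10^−6.

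**Other totals, equal clusters, exact distribution.** The article reports 63 eligible patients in one month (95% CI 50 to 77). Multiplying by 4:

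| Participants in 4 months | Basis | Expected non-empty | Red | Amber | Green |
|---|---|---|---|---|---|
| 160 | target | 69.3 | 80.6% | 19.4% | <0.001% |
| 200 | 50 per month | 73.5 | 17.0% | 82.9% | 0.05% |
| 252 | 63 per month | 76.6 | 0.3% | 97.2% | 2.5% |
| 308 | 77 per month | 78.3 | <0.01% | 82.7% | 17.3% |

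**Unequal clusters.** The article gives no coefficient of variation (CV) of cluster size, so these values are assumed (gamma-distributed sizes, simulated). Where two figures appear, the total was either held fixed or allowed to vary as Poisson.

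| CV | P(red) at 160 | P(red) at 252 |
|---|---|---|
| 0.2 | 84 to 88% | 1 to 2% |
| 0.3 | 91 to 94% | 4 to 6% |
| 0.5 | 99% | 36 to 37% |

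**Recruitment needed for green.** Setting (1 − e^−m)^80 = 0.5 gives m = 4.75, or about 380 participants in 4 months for an even chance of green. Setting it to 0.9 gives about 531. Both lie above the 308 implied by the upper confidence limit.

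**The case against.** **Green is attainable.** Two participants in every cluster gives 80 of 80. That is correct: the thresholds are not arithmetically impossible, and the two rows do not strictly contradict each other. A reader might infer either; the documents support only a statement about probability. The planned mean of two is an average, and random arrival does not deliver exactly two everywhere.

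**The trial was forecast above its minimum.** At 63 per month red is rare with equal clusters (0.3%), so it would be wrong to say that the trial as forecast will most likely be red. Amber is the likely result. But amber triggers the same plan, and part of the surplus is meant to cover repeat presentations and opt-outs. The row must also behave sensibly at 160, because Table 2 itself calls that green.

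**The clusters were made similar in size.** This argues against the high CVs. It does not rescue the row, since equal clusters are the most favourable case and already give 81% red at 160.

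**The consequence is mild.** The remedial plan adds to promotion that was planned anyway, and the Trial Management Group decides its content. The termination discussion is worded in terms of overall recruitment, which corresponds to the individual row. This stands, and it limits the importance of the point.

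**Bias.** Because the remedial plan promotes the SVT guideline, which favours non-conveyance after successful treatment, a reader might infer that a false alarm would distort the primary comparison. The documents do not show this. Nothing suggests that promotion would differ between control and intervention clusters, and the model in the Data analysis section has a fixed effect for stage that absorbs a change common to all clusters.

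**Conclusion.** The concern holds as a calibration fault, of moderate importance. Under random arrival over 80 equal clusters, a trial exactly on its individual target scores red on the cluster row about 81% of the time (77% if the total also varies as Poisson) and green with negligible probability. At the forecast rate it scores amber about 97% of the time. The remedial plan is therefore the probable outcome at every recruitment rate that the article reports, and the row cannot separate a real cluster-level problem from chance. The result rests on chance arrival, which the article does not state; unequal sizes make it worse. The damage is a false operational alarm. Sample size, allocation, the primary analysis and the termination rule are untouched.

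**What to change.** Replace the fixed 80 / 72–79 / below 72 cut-offs with cut-offs taken from the distribution of non-empty clusters expected at 160 participants. With w_i as cluster i's share of activity, the expected count is Σ[1 − exp(−160 w_i)], to be compared with the observed count. The activity data needed were already collected when the clusters were formed. They describe general activity, so using them assumes that SVT cases are roughly proportional to it.

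Check any new cut-offs both on target (160) and at the boundary of individual red (128). Simply lowering the fixed numbers is not enough. For example, green at 64 or more, amber at 60 to 63 and red below 60 would score an on-target trial green 99% of the time with equal clusters. At 128 participants the expected count is 80 × [1 − (79/80)^128] = 64.0, so the same cuts would still score green about 58% of the time and red only about 5%. At 160 with an assumed CV of 0.5, green would fall to about 62%. Those cut-offs should not be adopted as they stand.

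The cost is one table row and a short calculation. No extra data or patients are needed, and the design and analysis do not change.

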#### Progress (RAG) criteria

The stepped wedge design is predicated on reliably recruiting the number of participants specified by the sample size calculation at each stage of the trial. Monthly recruitment will be monitored closely by the TMG and regularly reported to the TSC. Recruitment below target (amber or red criteria) will trigger a remedial plan by the TMG with promotion of the SVT guideline and trial awareness and feedback on missed cases (where a VM was indicated but not undertaken) in addition to the planned promotion of the trial (newsletters, posters, etc) and NIHR CRN support. Financial constraints would preclude significant trial prolongation and if, despite these measures, trial recruitment was less than 80% of our overall target for the first 4 months of the study, we propose discussion with the TMG, TSC and funder to consider trial termination or agreed modification.

### Data analysis

Analysis will be conducted according to a prespecified statistical analysis plan written by the trial statisticians, approved by an independent statistician on the TSC and made publicly available ahead of database lock.

Participant and cluster (ambulance stations) characteristics will be summarised using means and SD or medians and IQRs for continuous variables and numbers and percentages for categorical variables, by condition status (intervention vs control) and overall.

In the main analyses, outcomes will be analysed using the intention-to-treat principle, based on intervention status of the cluster at the time of the VM, irrespective of whether there was evidence of device use. Per-protocol analyses will also be undertaken. Repeat presentations of patients previously recruited will be excluded from the primary analyses but included in secondary analyses. The intervention effect will be estimated through fitting mixed effects (‘multilevel’) regression models that allow for the correlation between outcomes of patients from the same cluster (station). The models will include fixed effects for the intervention effect and time (stage) and a random effect for the cluster.

Given the nature of the primary outcome and normally well-recorded routine data to be used in the trial, it is not anticipated that there will be a significant quantity of missing data. The trial Research Paramedic will make every attempt to retrieve any missing data. Should any key outcome data remain missing, sensitivity analyses may be proposed, using a range of assumptions where necessary and consideration given to suitable imputation.

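### The stated model terms name neither the location strata and cluster size used to randomise nor a patient level for analyses with repeat presentations; adding them is cheap and the gain is small

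*Protocol article*

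**What the plan says.** All of this is in the protocol article.

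- **Randomisation.** The section on forming and randomising clusters allocates 80 clusters, 20 per step, by computer-generated sequences "stratified by location and balanced on cluster size".
- **Model.** The Data analysis section describes mixed effects "regression models that allow for the correlation between outcomes of patients from the same cluster (station"), and lists the terms: "The models will include fixed effects for the intervention effect and time (stage) and a random effect for the cluster".
- **Repeats.** The same section states: "Repeat presentations of patients previously recruited will be excluded from the primary analyses but included in secondary analyses". The sample size section expects them in number: "This will allow for repeat presentations (around 10% of all cases by the end of an SVT VM trial of similar duration").
- **Further detail.** The Data analysis section also says: "Analysis will be conducted according to a prespecified statistical analysis plan written by the trial statisticians". That plan is not at hand.

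**The concern.** Two features of the design have no counterpart in the listed terms.

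1. **Randomisation factors.** Stratifying by location and balancing on size pays off in precision when the analysis uses the same factors. A stepped wedge model with a small intracluster correlation draws heavily on comparisons between clusters within a stage, so stable differences between locations are not fully removed by comparing each cluster with itself. Leaving location and size out can waste some precision. It also leaves open a later choice between adjusted and unadjusted estimates.

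2. **Patient level.** Where one patient contributes several episodes, those episodes are likely to be correlated. A cluster random effect captures only the part shared by everyone at that station. If nothing else is added, standard errors in those secondary analyses may be too small.

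**Working it through.** **Inputs from the protocol article:** 80 clusters, 5 stages, 20 clusters crossing per step, 2 participants per cluster per stage (800 in all), control non-conveyance 10%, effect 10 percentage points, intracluster correlation (ICC) 0.01, two-sided 5%, about 10% repeats.

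**Assumptions (not in the document):** number and spread of location strata, spread of cluster sizes, within-patient correlation, and how repeats are spread over patients.

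**Step 1: reproduce the plan's figure.** The article says: "The sample size was calculated using formulae presented by Hussey and Hughes". With I = 80, T = 5 and X = 1 when a cluster has the device:

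- U = sum of X = 200
- W = sum of squared stage totals = 20² + 40² + 60² + 80² = 12,000
- V = sum of squared cluster totals = 20 × (1 + 4 + 9 + 16) = 600

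Variance of the effect = Iσ²(σ² + Tτ²) / [(IU − W)σ² + (U² + ITU − TW − IV)τ²] = 80σ²(σ² + 5τ²) / (4,000σ² + 12,000τ²).

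Here σ² is the within-cluster variance divided by 2, and τ² is the between-cluster variance. Taking total variance 0.1 × 0.9 = 0.09 and ICC 0.01 gives σ² = 0.04455 and τ² = 0.0009. The SE is 0.0304 and power is 90.8%, which agrees with the stated 90% at 800.

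**Step 2: upper bound on the gain from location.** Suppose location explained all between-cluster variance, so τ² = 0 after adjustment. The SE is then √(0.02σ²). The adjusted column gives two versions: total variance kept as residual, then only the within-cluster part kept. The variance 0.15 × 0.85 = 0.1275 uses the mean of the two arms' rates.

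| Total variance | ICC | SE, power unadjusted | SE, power with τ² = 0 |
|---|---|---|---|
| 0.09 | 0.01 | 0.0304, 90.8% | 0.0300, 91.5% to 0.0298, 91.8% |
| 0.1275 | 0.01 | 0.0362, 78.9% | 0.0357, 80.0% to 0.0355, 80.4% |

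The ceiling at the design ICC is 0.7 to 1.5 points, or about 1 power point. The level of power in the second row comes from the outcome variance chosen, which is a separate matter. Only the difference between columns counts here.

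**Step 3: how far the fitted model relies on comparisons between clusters.** With 10 participants per cluster, the random-intercept weight is 10 × 0.01 / (1 + 9 × 0.01) = 9.2%, so little of a stable cluster difference is removed. A purely within-cluster estimate has variance 80 × 5 × σ² / 12,000. With σ² = 0.99 × 0.1275 / 2 = 0.0631 this gives SE 0.0459. Its efficiency is (0.0362 / 0.0459)² = 62%. Comparisons between clusters matter, but they do not carry nearly all the information.

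**Step 4: simulation of the primary analysis.** There were 1,000 trials per setting, with four equal location strata, a between-location SD of 0, 2 or 4 points, unequal cluster sizes, and a linear mixed model with and without location and size.

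| | Without terms | With terms |
|---|---|---|
| Type I error | 4.8–5.6% | 4.9–5.4% |
| Power | 77–80% | 77–79% |
| Mean estimate (true 0.10) | 0.098–0.101 | 0.098–0.100 |

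**Step 5: repeats in secondary analyses.** With 800 first presentations and 10% repeats, episodes number 800 / 0.9 = 889, of which 89 are repeats. The design effect is 1 + ρ × Σ(n² − n) / Σn, where n is a patient's number of episodes and ρ the assumed within-patient correlation.

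- Each repeat from a different patient (89 pairs): 178 / 889 = 0.200. For ρ = 0.1 to 0.8 the design effect is 1.02 to 1.16, and the naive SE is 1% to 7% too small.
- Repeats concentrated (30 patients with 4 episodes each): 360 / 890 = 0.404. The design effect is 1.04 to 1.32, and the naive SE is 2% to 13% too small.

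This formula treats all of a patient's episodes as contributing to the same comparison. Simulation of the stepped wedge itself put the true SE about 3% to 12% above the naive one when a patient's episodes stay in one cluster, and about 0% to 1% above when they do not. A second simulation, with latent within-patient correlation 0.6 to 0.8, gave ratios of true to naive SE of 0.98 to 1.05.

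**The case against.** The strongest reply is that this is analysis plan content. The article defers to a prespecified plan, says what the models will include without saying that the list is complete, and names the terms that match its sample size method. That stands in part. A reader might infer that the models contain only these three terms, or that repeat episodes will be treated as independent. The text says neither, and the unseen plan may add terms. What remains is that the article does state a model, and the stated terms do not reflect its own randomisation and data structure. Naming the missing terms is therefore a concrete improvement to a stated model.

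A second reply is that stratification itself limits location imbalance, so leaving the factor out should not bias the estimate. That stands, and the simulation agrees. A reader might also infer a larger loss, such as power rising from 76% to 80% on adjustment. That contrast needs an ICC of 0.05. The article gives an estimate of 0.009 and a design value of 0.01.

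A third reply is that repeats leave the primary result untouched. That is correct. The upper end of the range for secondary analyses also needs both a strong correlation and repeats concentrated in few patients, neither of which the article gives.

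**Conclusion.** The point holds as a low-cost improvement. The listed terms do not name location stratum or cluster size, and no patient-level term is named where repeats enter.

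- **Primary analysis:** the gain from adjustment is at most about 1 power point at ICC 0.01. No bias or type I error problem was shown, under four assumed strata and the assumed spreads.
- **Secondary analyses with repeats:** naive standard errors could be from about 0% to 13% too small. The size depends on the assumed within-patient correlation (0.1 to 0.8), on how concentrated the repeats are, and on whether a patient's episodes fall in the same cluster.

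The argument for change is consistency with the design and a choice fixed in advance. No figure in the article is wrong on this point.

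**What to change.** Extend the model sentence in the Data analysis section, and carry the same wording into the analysis plan before unblinding:

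- Add location stratum (fixed effect) and cluster size to the primary and secondary models. Report the model with stage and cluster only as a sensitivity analysis.
- In any analysis that includes repeat presentations, use a patient random effect or standard errors robust to several episodes of one patient. The method should allow for a patient being treated by different clusters.

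If the analysis plan already does this, a cross-reference is enough. The cost is a sentence or two and a few degrees of freedom, with 80 clusters available. No new data are needed: location and size were used to randomise, and repeat patients must already be identified to exclude them from the primary analysis.
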